## Abstract

**Background:**

In the clinical setting, a large proportion of children with an autism spectrum disorder (ASD) experience anxiety symptoms. Because anxiety is an important cause of impairment for children with an ASD, it is necessary that effective anxiety interventions are implemented for these children. Recently, a serious game called Mindlight has been developed that is focused on decreasing anxiety in children. This approach is based on recent research suggesting that video games might be suitable as an intervention vehicle to enhance mental health in children. In the present study it will be investigated whether Mindlight is effective in decreasing (sub) clinical anxiety symptoms in children who are diagnosed with an ASD.

**Methods/Design:**

The present study involves a randomized controlled trial (RCT) with two conditions (experimental versus control), in which it is investigated whether Mindlight is effective in decreasing (sub) clinical anxiety symptoms in children with an ASD. For this study, children of 8–16 years old with a diagnosis of an ASD and (sub) clinical anxiety symptoms will be randomly assigned to the experimental (N = 60) or the control (N = 60) condition. Children in the experimental condition will play Mindlight for one hour per week, for six consecutive weeks. Children in the control condition will play the puzzle game Triple Town, also for one hour per week and for six consecutive weeks. All children will complete assessments at baseline, post-intervention and 3-months follow-up. Furthermore, parents and teachers will also complete assessments at the same time points. The primary outcome will be child report of anxiety symptoms. Secondary outcomes will be parent report of child anxiety, child/parent report of depressive symptoms, and parent/teacher report of social functioning and behavior problems.

**Discussion:**

This paper aims to describe a study that will examine the effect of the serious game Mindlight on (sub) clinical anxiety symptoms of children with an ASD in the age of 8–16 years old. It is expected that children in the experimental condition will show lower levels of anxiety symptoms at 3-months follow-up, compared to children in the control condition. If Mindlight turns out to be effective, it could be an important contribution to the already existing interventions for anxiety in children with an ASD. Mindlight could then be implemented as an evidence-based treatment for anxiety symptoms in children with an ASD in mental health institutes and special education schools.

**Trial registration:**

Dutch Trial Register NTR5069. Registered 20 April 2015.

## Background

In the clinical setting, a large proportion of children with an autism spectrum disorder (ASD) experience anxiety symptoms. Between 11 % and 84 % of all children with an ASD experience some degree of impairing anxiety [1]. More specifically, 21 % of the children with an ASD suffer from subclinical anxiety [2] and approximately 40 % of the children with an ASD meet the criteria of at least one anxiety disorder [3]. Some of the most frequently reported anxiety disorders and symptoms seen in children with an ASD are simple phobias, generalized anxiety disorder, separation anxiety disorder, obsessive-compulsive disorder and social phobia [1].

Moreover, anxiety is an underlying cause of several symptoms of ASD. For example, anxiety underlies or affects the stereotype and rigid behavior [4] and the problems in social functioning [5] that children with an ASD often show. Anxiety also underlies comorbid symptoms of children with an ASD, for example oppositional and aggressive behavior [6] and depressive symptoms [7]. Furthermore, anxiety in children with an ASD has a negative impact on adaptive functioning, daily living skills and relationships with peers, teachers and family [8–10]. Therefore, it is important that anxiety in children with an ASD is treated and prevented from further escalation.

Recognition of anxiety symptoms in children with an ASD is not new. In the original description of children with an ASD, Kanner [11] stated that a number of these children had “substantial anxiety problems”. Yet, the evaluation and treatment of anxiety in children with an ASD has only recently received empirical attention [1]. Many studies showed the effectiveness of adapted versions of cognitive behavioral therapy (CBT; *e.g.* [12]) or new interventions especially developed for children with an ASD (*e.g.* [13]), reasoning that the traditional form of CBT is not suitable for children with an ASD. On the other hand, a recent study of Van Steensel and Bögels [14] has shown that CBT is effective in reducing anxiety symptoms in children with an ASD, and that CBT is as effective for children with an ASD as for children without an ASD.

However, there are some important limitations to CBT for anxiety, both in general and specifically for children with an ASD. First, CBT largely consists of teaching children to become conscious of their negative thoughts, to evaluate these thoughts, and eventually to challenge them and formulate thoughts that are more accurate. These sessions have a face-to-face, verbal and cognitively complex character. Because children with an ASD have a cognitive and social impairment, they have difficulties with learning skills in these CBT-sessions and as a result they are often not intrinsically motivated for CBT [15]. Therefore, a greater focus on visual aids and structured sensory information is an important requirement in anxiety treatment for children with an ASD [15, 16]. Second, there is a large gap between the knowledge that children gain in CBT and the implementation and practice of this knowledge in daily life. Especially for children with ASD, frequent practice and exposure opportunities are important in anxiety interventions [1]. However, the exercises in CBT that do exist are mostly de-contextualized and do not fully represent the situations in which children experience their anxiety. A third limitation of CBT is limited access to care and long waiting lists to care that is accessible [17]. Finally, the low cost effectiveness is a limitation of CBT, which many mental health institutions experience as a barrier to treatment delivery. Therefore, it is important that new anxiety interventions are developed that can provide a solution for the above mentioned limitations.

Recently, it has been shown that video games have the potential to enhance mental health and well-being in children and adolescents [18, 17]. For example, Merry *et al.* [19] found that the video game ‘SPARX’ was effective in reducing depressive symptoms among adolescents in the age between 12–19 years old. They concluded that it was a potential alternative to usual care for adolescents with depressive symptoms in primary care settings and that it could be used to address some of the unmet demands for treatment. More recently, the serious game Mindlight (Playnice Institute) has been developed for the treatment of anxiety disorders in children. A recent study has tested the effect of Mindlight on anxiety symptoms in school children [20]. This study showed that both the anxiety of the children who played Mindlight as the anxiety of the children who played the control game significantly decreased over time. However, no studies to date have investigated the effect of a serious game on anxiety symptoms of children with an ASD.

Mindlight has the aim to tackle anxiety in children by using several treatment mechanisms. First of all, it uses exposure techniques, one of the most empirically-validated treatment components of CBT for anxious individuals [21]. During exposure, individuals are gradually exposed to the threatening cues. In this way, they are getting habituated to these cues and eventually they are getting more comfortable and less anxious when being exposed to them. Moreover, Mindlight uses neurofeedback mechanisms, which is effective in decreasing anxiety symptoms of children [22]. These mechanisms are focused on regulating arousal levels associated with anxiety through relaxation and concentration. Finally, attention bias modification is incorporated in Mindlight, which is a therapy mechanism in which children learn to (a) disattend to threatening cues and shifting attention away from those cues and to (b) focus on positive aspects of the environment in the service of relevant goals [23].

It is hypothesized that Mindlight has the potential to serve as an effective new intervention for children with ASD and comorbid (sub) clinical anxiety symptoms, and that it can overcome the limitations of CBT. First, it is known that children with ASD often feel a close affinity for technology and games, which means that the participating children are probably intrinsically motivated to play a game like Mindlight in therapy [24]. Moreover, it has been reported that computer based training could be an effective tool in treatment for children with ASD, due to its visual and structured character [15]. Mindlight uses visual aids and structured sensory information to a great extent, both for creating a ‘scary’ exposure environment and for teaching important treatment concepts. Furthermore, Mindlight includes frequent practice and exposure opportunities. Because Mindlight can be played repeatedly, with the difficulty level increasing as children become better players, there is a great deal of practice and exposure involved in playing this game. As a result, the gap between knowledge and behavior may be substantially decreased and effective cognitive and emotional coping skills can be automatized and possibly generalized with practice. Finally, therapy skills can be practiced at home, which means that children have an easier access to mental health care. In this way, the waiting lists can become shorter and the therapy costs can be decreased when implementing a game like Mindlight as therapy tool.

In the present study, the primary aim is to investigate whether Mindlight is effective in reducing (sub) clinical anxiety symptoms in children with an ASD. The secondary aim is to examine whether Mindlight is effective in reducing parent report of child anxiety, and the anxiety-related depressive symptoms, social functioning and behavior problems of the participating children. To investigate these aims, a multi method symptom assessment is used, including parent, teacher and child reports [1]. If Mindlight turns out to be effective for anxious children with an ASD, it could be considered as a new therapeutic intervention next to the already existing approaches for anxiety in children with an ASD.

## Methods

The study design will be reported in line with the CONSORT 2010 Statement for reporting parallel group randomized trials [25]. The medical ethics committee CMO Arnhem-Nijmegen in the Netherlands has given approval for the conduction of this study (NL50023.091.14). Moreover, the study is registered in the Dutch Trial Register for RCT’s (NTR5069).

### Design

The present study involves a randomized controlled trial (RCT) with two conditions (experimental versus control), in which it is investigated whether the new video game Mindlight is effective in treating (sub) clinical anxiety symptoms in children with an ASD. For this study, children in the age of 8–16 years old with a diagnosis of an ASD according to the Diagnostic and Statistical Manual of Mental Disorders 4th Edition – Text Revision (DSM-IV-TR; [26]) will be screened for anxiety symptoms. The children with (sub) clinical anxiety symptoms will be selected and approached for participation.

After the selection and recruitment, children will be randomly assigned to the experimental or control condition. At baseline (T0), children, parents and teachers will fill in questionnaires. Moreover, parents will undergo a semi-structured interview (ADIS-P; [27]) to determine whether their child meets the criteria of one or more anxiety disorders. At post-intervention (T1) and at 3-months follow-up (T2), children, parents and teachers will fill in questionnaires again to evaluate the effect of Mindlight. At 3-months follow-up, parents will undergo the semi-structured interview again to test whether Mindlight also had an effect on the present anxiety disorder (s) in the participating children. Fig. 1 shows a schematic overview of the design in the present study.

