**Fig. 1 Fig1:**
[figure not shown]
Flow diagram of recruitment, randomization and assessments. FU = Follow-up

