### Participants’ eligibility

Children with an ASD (DSM-IV-TR: Autistic disorder, Asperger disorder, PDD-NOS; [26]) in the age between 8 to 16 years old will be assessed for eligibility by a screening. This screening consists of filling in an anxiety questionnaire by both children (SCAS-C; [28]) and parents (SCAS-P; [29]). When children have at least subclinical levels of anxiety, they are eligible for participation in the study. Moreover, they have to have sufficient knowledge of the Dutch language. Exclusion criteria are absence of parental permission and presence of prominent suicidal ideation or other severe psychiatric problems that need immediate treatment (*e.g.* severe trauma’s).

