### Procedure

Contexts of recruitment are mental health institutes (*e.g.* GGZ Oost Brabant) and special education schools in the Netherlands. First, parents will receive a letter with information about the screening and the study. Moreover, children and parents will be asked to fill in the SCAS-C/P [28, 29]. When children have at least subclinical levels of anxiety and meet the other inclusion criteria, children and parents will be approached to participate in the study. If children and parents agree with participation, active written informed consent of the parents and the children who are above the age of 12 will be obtained.

After obtaining active written informed consent, children will be randomly allocated to the experimental or control condition. Children in the experimental condition will play Mindlight individually for one hour per week during 6 consecutive weeks at the recruitment location. Moreover, children may receive treatment as usual (TAU) parallel with Mindlight. TAU will mainly be offered by mental health institutes and might for example consist of psycho-education on ASD, play/drama therapy, parent guidance and/or medication. These types of TAU will be monitored and reported during the course of the study, and will be tested as potential confounders in the analyses. Children in the control condition will play the computer game Triple Town individually for one hour per week during 6 consecutive weeks at the recruitment location. Again, children may receive TAU parallel with the game. Moreover, they will have the opportunity to play Mindlight after the 3-months follow-up if this game turns out to be effective.

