### Data analysis/statistical analysis

Following the intention-to-treat principle [48], all children randomized to a condition will be included in the analyses to test the study objectives. Multiple imputations will be used for missing observations at post-intervention and 3-month follow-up. Reporting of the results of the study will be in accordance with the CONSORT 2010 Statement [25].

To investigate the differences in the development of anxiety symptoms between children in the experimental condition and children in the control condition, a 3 (within-subjects: pre, post, follow-up) by 2 (condition: experimental vs. control) ANOVA (repeated measures) will be conducted, with anxiety symptoms (child report) as the dependent variable. The direct effect of Mindlight on parent report of child anxiety, parent/child report of depressive symptoms, and parent/teacher report of social functioning and behavior problems will be investigated in the same way. Furthermore, remission rates of the anxiety disorders that were diagnosed at baseline (with ADIS-P) will be calculated at 3-months follow-up, and Chi-square (*χ*^2^) tests will be conducted to compare remission rates between the experimental and control group. In the above mentioned analysis plan it is assumed that the children will play the game individually and that therefore the data will not be clustered. However, in case of clustered data due to the formation of groups in which several children play the game in the same room, the analyses will be conducted in MPLUS 6.11 [49].

Finally, possible baseline differences between the two conditions in demographic variables (*e.g.* age, sex, educational level), anxiety symptoms, gaming behaviour and treatment expectancies will be checked. Moreover, possible differences in TAU between the experimental and control condition will be checked at all time points. Variables that show different distributions between the two groups will be entered as confounders in all models testing the effectiveness of the intervention.

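### As described, randomisation precedes the T0 assessments and no masking at T0 is stated, so T0, and above all the ADIS-P that defines the remission denominator, is not protected from the allocation

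*Protocol article*

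**What the plan says.** The Design section describes screening and selection and then states: "After the selection and recruitment, children will be randomly assigned to the experimental or control condition. At baseline (T0), children, parents and teachers" fill in questionnaires. The baseline ADIS-P interview with the parents follows, then post-intervention (T1) and three-month follow-up (T2).

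The Procedure section gives the same place to randomisation relative to consent: "After obtaining active written informed consent, children will be randomly allocated to the experimental or control condition". It then goes on to the game sessions and mentions no assessment in between. The caption of Fig. 1 reads "Flow diagram of recruitment, randomization and assessments"; the figure itself is not visible in the text at hand.

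Before allocation, the only outcome measures described are the child and parent anxiety scales: "This screening consists of filling in an anxiety questionnaire by both children (SCAS-C; [28]) and parents (SCAS-P; [29". According to Table 1, the ADIS-P, CDI 2, VISK, SDQ and PETS are first taken at T0.

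The analysis section uses T0 in three ways:
- as the first level of the primary model: "a 3 (within-subjects: pre, post, follow-up) by 2 (condition: experimental vs. control) ANOVA (repeated measures) will be conducted";
- to define who can remit: "remission rates of the anxiety disorders that were diagnosed at baseline (with ADIS-P";
- to compare anxiety symptoms and treatment expectancies between arms, with variables that differ entered as confounders in all effectiveness models.

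**The concern.** A baseline is safe from the allocation when it is recorded before randomisation, or when those who supply it do not know the result. The article gives neither assurance. Every T0 measure is a rating by child, parent or teacher, or a judgement by an interviewer, so knowledge of the allocation could move it.

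Three uses of T0 would suffer if that happened. A difference between arms at T0 caused by the allocation would enter the comparison of development over time as if it were treatment effect, or would hide one. The group counted as having an anxiety disorder at baseline could differ between arms for reasons other than chance, so the chi-square comparison of remission would rest on a subgroup formed after randomisation. And PETS scores given with knowledge of the assigned game would be a consequence of allocation; adjusting for them as confounders could remove part of the effect under study.

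**Working it through.** **1. Order of events, section by section**

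| Place | Randomisation | T0 |
|---|---|---|
| Design | after selection and recruitment | described in the sentences that follow |
| Procedure | directly after consent | not mentioned |
| Fig. 1 caption | listed second | assessments listed third; not conclusive, because screening assessments precede randomisation |

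No section puts T0 first. Only the Design section mentions both steps, and there the order is read from the sequence of sentences.

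**2. Who could know the allocation at T0**

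The Intervention section has the game explained to the child in session 1. It does not say when parents, teachers or interviewers learn the allocation. The ADIS-P interviewers and the session leaders come from the same staff categories (qualified therapists, or master students under their supervision), and no separation of the two roles is stated. The ADIS-P decision on presence of a disorder rests on the interviewer's clinical judgement of severity.

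**3. Which measures have a fallback before randomisation**

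The SCAS-C (primary outcome) and SCAS-P do, from screening. The ADIS-P, CDI 2, VISK, SDQ and PETS do not. The planned analyses do not use the screening score as the baseline.

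**4. The plan's own figure**

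The sample size does not depend on this point, but it reproduces. For the between-groups test of a repeated-measures ANOVA with f = 0.25, m = 3 measurements and an assumed correlation ρ = 0.5 (not stated in the article), the noncentrality is λ = f²·N·m / (1 + (m − 1)ρ) = 0.0625 × 86 × 3 / 2 = 8.06. This gives power 0.8015 at N = 86. Then 86 × 1.40 = 120.4, that is 120. For two equal groups, f = 0.25 corresponds to d = 2f = 0.5.

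**5. Illustration of what a shift would do**

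The article gives neither a shift nor a correlation, so both are assumed. Suppose there is no true effect and that knowledge of the allocation moves T0 by s SD in one arm only. The T0-to-T2 change contrast is then biased by s. Its standard error in SD units is √(2(1 − r)) × √(2/n). With n = 60 per arm this is 0.1826 for r = 0.5 and 0.1414 for r = 0.7. The two-sided type I error is 1 − Φ(1.96 − s/SE) + Φ(−1.96 − s/SE):

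| s (assumed) | r = 0.5 | r = 0.7 |
|---|---|---|
| 0 | 0.050 | 0.050 |
| 0.1 | 0.085 | 0.109 |
| 0.2 | 0.195 | 0.293 |
| 0.3 | 0.376 | 0.564 |

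With 48 per arm (60 × 0.8, the planned 20 % loss) and r = 0.5, the values for s = 0.1, 0.2 and 0.3 are 0.078, 0.165 and 0.312.

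Relative to d = 0.5, shifts of 0.1 and 0.2 are 0.1/0.5 = 20 % and 0.2/0.5 = 40 %. These percentages only restate the assumed shift and are no evidence that one occurs. No comparable figure can be given for remission, because the article states no expected number of diagnoses.

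**The case against.** The strongest reply is that the order is inferred. The Design section may simply state the allocation and then list the assessment schedule; the Procedure section is silent on T0; and Fig. 1, to which the reader is sent for the schematic, is not visible and may settle the matter. That stands as a limit on certainty. It does not remove the point, because all of the visible text that gives an order gives the same one.

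A reader might infer that T0 is invalid as a baseline. The document does not support that. T0 appears to precede the game sessions, and it is biased only if respondents or interviewers know the allocation by then, which is nowhere stated. The one disclosure step described, the explanation of the game in session 1, leaves room for T0 to have been completed in ignorance of it.

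It is also fair that the primary outcome has a screening measurement before randomisation, that a straight comparison of arms at T2 would not use T0, and that PETS enters a model only if its distribution differs between arms. These limit the damage for the SCAS-C and SCAS-P. They do not help the ADIS-P, for which there is no earlier interview, and the planned ANOVA does include T0.

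The timing of disclosure could be called operational detail left to the full protocol. That would be a sufficient answer if the article were silent on the order. It describes one, and following it would form the remission subgroup after randomisation through a judgement-based interview with no stated masking.

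**Conclusion.** The point holds in a limited form. As described, T0 follows randomisation, and nothing stated protects it from knowledge of the allocation. Freedom from such influence is not assured; actual bias is not demonstrated, and neither its direction nor its size can be derived from the document. The type I error figures in the working depend entirely on the assumed shift and correlation.

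The exposure is greatest for ADIS-P remission, a secondary analysis. It is moderate for the primary ANOVA, where a screening SCAS-C offers a fallback, and conditional for the use of PETS in selecting confounders. The conclusion rests on reading the order of the Design text as chronological. If Fig. 1 or the full protocol places T0 before allocation, one clarifying sentence settles the point.

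**What to change.** State, and follow, this order: consent; all T0 child, parent and teacher questionnaires and the ADIS-P; then randomisation. If randomisation has to come first for practical reasons, withhold the allocation from families, teachers and ADIS-P interviewers until T0 is complete, and say so.

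For any child already randomised before T0, add a sensitivity analysis of the primary outcome with the screening SCAS-C as the baseline. Do not adjust for PETS where it was collected after the allocation was known; report it descriptively. Remission has no equivalent repair, since no ADIS-P exists before T0, so its report should say whether the interview came before or after allocation and whether the interviewer knew the result.

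The cost is a procedural amendment and a short delay between consent and allocation. No new measures are needed, and the sample size does not change.
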